### The common technique in the LAP-CME and cLAP groups

In the two control groups the position of the patient, the chief surgeon, first assistant, second assistant, and monitor will be the same as described for the experimental group. A five-trocar technique is usually used (Fig. 5a). A camera port (trocar A) will be created through a supraumbilical 10-mm incision and a pneumoperitoneum of 12–15 mmHg will be established through the camera port. Another four transabdominal trocars will also be placed under laparoscopic visualization: two 12-mm trocars (trocars B and C) in the right and left lower quadrant as the surgeon’s dominant operation channel; another 12-mm trocar (trocar D) as the assistant’s dominant operation channel; one 5-mm trocar (trocar E) under the xiphod as the assistant’s nondominant operation channel.

**Fig. 5 Fig5:**
[figure not shown]
Trocar positions and surgical procedure for the control intervention group. **a** Trocar positions for LAP-CME and cLAP groups. Trocar A = 10 mm, Trocars B–D = 12 mm, Trocar E = 5 mm. **b** The transverse is divided under laparoscopy in the LAP-CME group. **c** The distal ileum is divided under laparoscopy in the cLAP group. **d** The terminal of the SMV is identified under laparoscopy and D3 lymphadenectomy is performed along the SMV in the cLAP group

### The different technique in the LAP-CME and cLAP groups

In the LAP-CME group the transverse colon and distal ileum will be firstly divided at the elected sites of resection under laparoscopy, and then the terminal of the SMV will be identified and the ileocolic vessels will be ligated (Fig. 5b). D3 lymphadenectomy along the left side of the SMV in a repeated unidirectonal/longitudinal manner and removing the cancer-bearing segment from the medial to lateral under laparoscopy are similar to the HALS-CME group. The specimen will be dragged out through the midline incision around trocar A and an end-to side anastomosis will be fashioned extracorporeally.

In the cLAP group, after establishing the pneumoperitoneum and exploring the abdomen, the terminal of the SMV will be identified under laparoscopy; the method of D3 lymph node dissection is same as in the HLAS-CME and LAP-CME groups (Fig. 5c and d). After the ileocolic vascular pedicle, right colon vascular pedicle, and middle colon vascular pedicle ligation, the cancer-bearing segment will be removed from the medial to lateral. The involved segment will be dragged out through the midline incision around trocar A. The transverse colon and distal ileum will then be ligated, and an end-to-side anastomosis will be fashioned.

## Blood and peritoneal wash collection

### Blood sample collection

Blood samples from the peripheral blood and SMV will be collected from patients at two different time points (Fig. 6a). After exposing the distal SMV both in the experiment and control groups, blood samples will be extracted simultaneously from the SMV and peripheral vein. The second time point is at after handling the Henles’ trunk and before the mobilization of the cancer-bearing segment. To prevent any contamination of epithelial cells, the initial 2 ml of blood will be discarded from all blood samples and the following 10 ml of blood will be used for RNA extraction. The SMV blood sample will be extracted using our home-made device under larparoscopy (Fig. 6b). Density gradient centrifugation techniques will be used to collect cells.

**Fig. 6 Fig6:**
[figure not shown]
Blood and peritoneal wash collection. **a** Timeframe for collecting blood samples and peritoneal washes. **b** SMV blood is collected using our home-made device under laparoscopy. *PV* peripheral vein, *SMV* superior mesenteric vein

### Peritoneal wash collection

Peritoneal washes will also be collected at two different time points during the operative period. At the beginning of each operation, 100 ml saline will be introduced into the hepatorenal recess and the Douglas cavity and aspirated after gentle stirring. After complete mobilization of the cancer-bearing segment, another 100-ml peritoneal wash will be aspirated after gentle stirring. Each peritoneal wash will be used for RNA extraction. After the peritoneal washes are centrifuged for 10 min at 1000 × g, cells will be collected and rinsed with phosphate-buffered saline (PBS), dissolved in TRIzol RNA extraction buffer (Invitrogen, Carlsbad, CA, USA), and stored at –80 °C.

### Quantitative TaqMan RT-PCR

Total RNA will be extracted through a guanidinium-isothiocyanate-phenol-chloroform-based method. Complementary DNA (cDNA) will be synthesized from total RNA by a PCR instrument Veriti Dx (Applied Biosystems) according to the manufacturer’s instructions. In this reaction, 2 μg total RNA, 4 μl 5× miScript HiSpec Buffer, 1 μl 10× Nucleics Mix, 2 μl miScript Reverse Transcriptase Mix, and no RNA enzyme water will be run in a total reaction volume of 20 μl and incubated at 37 °C for 60 min and 95 °C for 5 min. Two-step RT-PCR with TaqMan probe of CEA, CK20, and Beta-actin will be performed using an Applied Biosystems ViiA7 Real-time PCR System. The probe for CEA and CK20 is ACTB-Taqman, 5’-TGTACGTTGCTATCCAGGCT-3’; primers for CEA, CK20 are as follows: CEA, forward primer, 5’-CAATCTGCCCCAGCATCTTT-3’; reverse primer, 5’-CGGTTGCCATCCACTCTTTC-3’; CK-20, forward primer, 5’-GCAACAGGTCACAGTGAATA3-3’; reverse primer, 5’-CTCAGCTCCGTTAGTTGAAC-3’. The PCR solution (16 μl) will be composed of 1 μl cDNA solution, 2 μl of the forward and reverse primers, 1 μl Taqman probe, 8 μl Taqman Universal Master Mix II (Applied Biosystems), and water to adjust the final volume in each reaction. All reactions will be incubated in a 384-well plate at 95 °C for 6 min, followed by 45 cycles of 95 °C for 10 s, 60 °C for 10 s, and 72 °C for 30 s. All samples will be performed in triplicate. The actin gene will be used as a control to normalize differences in total RNA levels in each sample. The relative amount of each mRNA to actin RNA will be expressed using the equation 2^–ΔΔ^CT, where ΔΔCT = (ΔCt mRNA – ΔCt actin). E﻿xample template of recommended content for the schedule of enrolment, interventions, and assessments is shown in Fig. 7.

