## Outcome measures

### Primary outcomes

The primary endpoints are safety, efficacy, and being oncologically clear. Perioperative morbidity will be divided into intraoperative morbidity observed during the operation and postoperative morbidity observed during the hospital stay and within 30 days at the outpatient clinic. Postoperative morbidity will be assessed according to the Clavien-Dindo classification. Real-time polymerase chain reaction (RT-PCR) will be used to test whether the novel total “no-touch” isolation technique could potentially reduce tumor cells shedding into the portal circulation, peripheral circulation and peritoneal cavity. Other primary outcomes include 3-year disease-free survival (DFS), progression-free survival (PFS), overall survival (OS), and recurrence pattern (local recurrence, metastasis).

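### The RT-PCR text assigns the actin probe to both tumour markers, against its own preceding sentence, and labels the reported quantity so that a level and a change cannot be told apart

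*Protocol article*

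**What the plan says.** The Primary outcomes section of the protocol article includes the molecular test: RT-PCR "will be used to test whether the novel total" no-touch technique reduces shedding of tumour cells into the portal blood, the peripheral blood and the peritoneal cavity.

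The section Quantitative TaqMan RT-PCR gives the method:

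- Probes in use: "Two-step RT-PCR with TaqMan probe of CEA, CK20, and Beta-actin will be performed".
- Probe as specified: "The probe for CEA and CK20 is ACTB-Taqman", followed by one sequence. No other probe sequence is printed.
- Primers: "primers for CEA, CK20 are as follows", with one forward and one reverse sequence for each of these two markers.
- Role of actin: "The actin gene will be used as a control to normalize differences in total RNA levels in each sample".
- Reported quantity: "The relative amount of each mRNA to actin RNA will be expressed using the equation" 2^-ΔΔCT, where ΔΔCT is a ΔCt for the mRNA minus a ΔCt for actin. Neither ΔCt is defined, and no calibrator sample is named.

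The sections on blood and peritoneal wash collection take each kind of specimen at two time points during the operation.

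**The concern.** A TaqMan probe reports a gene only if it binds within the product made by that gene's primers. An actin probe used with CEA or CK20 primers has nothing to bind to, so the sentence that specifies the probe describes reactions that cannot detect either marker. It also conflicts with the sentence before it, which provides for a probe of each gene.

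The equation raises a separate question. The words describe an amount relative to actin within one sample. The symbol ΔΔCT normally denotes that amount compared again with a calibrator sample. Because two samples per patient are taken at each site, the first sample is an obvious candidate for the calibrator. A reader cannot tell whether the arms will be compared on the level at each time point or on the change between time points.

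This assay is how the trial measures tumour-cell shedding, which is the proposed mechanism of the no-touch technique. An error in its specification therefore reaches a listed primary outcome in all three arms.

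**Working it through.** The protocol article states no figure for this outcome that could be reproduced. The check compares sentences and then evaluates the equation under its possible readings.

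**Probe**

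1. Genes said to have a probe: CEA, CK20, beta-actin (three).
2. Probe sequences printed: one, labelled ACTB.
3. Genes to which that sequence is assigned: CEA and CK20.
4. Gene used for normalisation: actin.

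Items 1 and 3 cannot both hold. If item 3 is followed, neither marker has a matching probe. Per patient there are four blood samples (peripheral vein and superior mesenteric vein, two times each) and two washes, so 4 + 2 = 6 samples. With two markers, 6 × 2 = 12 marker results per patient would be affected. The printed sequence was not checked against a gene database; that it is actin rests on the document's own label.

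**Equation**

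Assumed Ct values, for illustration only:

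- first sample: target 34, actin 20
- second sample: target 32, actin 20.5
- external fixed calibrator: target 30, actin 20

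Value reported for the second sample:

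- (A) Level, no calibrator: 2^-(32 - 20.5) = 2^-11.5 = 0.000345
- (B) Relative to the fixed calibrator: 2^-[(32 - 20.5) - (30 - 20)] = 2^-1.5 = 0.354
- (C) Relative to the patient's own first sample: 2^-[(32 - 20.5) - (34 - 20)] = 2^2.5 = 5.66

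The printed form also fits (C). If each ΔCt is the change in one gene from first to second sample, then ΔCt for the mRNA is 32 - 34 = -2 and ΔCt for actin is 20.5 - 20 = 0.5. The exponent is -2 - 0.5 = -2.5, which again gives 2^2.5 = 5.66. If instead the inner Δ signs are surplus, the same expression is (A). The notation does not decide between them.

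**Does the choice matter for the test?**

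(A) and (B) differ by the constant factor 2^10 = 1024 for every patient. A constant factor leaves the t test and the Mann-Whitney test unchanged. (C) subtracts each patient's own first value and so tests something else.

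One simulated data set illustrates this. It assumes two arms of 50, second-sample ΔCt means of 12 and 11, first-sample means of 13 in both arms, SD 2 throughout, and first and second samples independent.

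| Reading | Mann-Whitney p | t test p |
|---|---|---|
| A | 0.0014 | 0.120 |
| B | 0.0014 | 0.120 |
| C | 0.0129 | 0.648 |

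The p-values are from a single draw and predict nothing about this trial. They show only that A and B agree exactly and that C is a different analysis.

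**The case against.** The best defence is that the section, read as a whole, describes a sound three-gene assay with one garbled line. It provides for three probes, prints separate CEA and CK20 primers and normalises to actin. A label or line lost in drafting would explain the conflict. That is plausible, and it limits the conclusion. A reader might infer that the primary RT-PCR outcome cannot be produced at all. The documents do not support this, because the preceding sentence provides for the marker probes. The defence does not remove the contradiction, however: the only probe the article specifies is assigned to the wrong genes.

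On the equation, the defence is that the words fix the quantity as marker relative to actin, with one subtraction, so it can be computed as 2^-ΔCt and needs no calibrator. A fixed calibrator would cancel between arms in any case. This also stands. The missing calibrator does not block the outcome. What remains is a mislabelled quantity, whose printed form equally fits a change from the first sample.

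Four further inferences should not be drawn:

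- **Marker-to-actin ratio near 1 everywhere.** This would require the marker wells to measure actin. The listed CEA and CK20 primers do not produce an actin product, so the literal reading gives no signal.
- **Loss of sensitivity at reverse transcription.** The entry "1 μl 10× Nucleics Mix" works out at 10 × 1/20 = 0.5× in the 20 μl reaction. It concerns one component of a step run to manufacturer's instructions that are not shown, and no loss is demonstrated.
- **Missing actin primers, or the stray character in the CK20 forward primer.** An article may leave the first to a fuller document. The second is clerical.
- **Lack of a rule for undetected samples.** That is commonly settled in an analysis plan or laboratory manual.

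**Conclusion.** The point holds in limited form. On the measurement of a listed primary outcome, the assay section contradicts itself about which probe belongs to which gene. Taken literally, the probe sentence gives no marker-specific signal for CEA or CK20 in any sample or arm. This rests on the document's ACTB label and on the ordinary working of TaqMan probes. It does not establish what the laboratory actually does.

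The equation fault is smaller. The quantity described can be computed, but its label leaves open whether a level at each time point or a change from the first sample is compared. Under the assumed Ct values these are 0.000345 and 5.66 for the same sample. The values depend on the assumptions; the difference in what is tested does not.

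The other primary outcomes, the randomisation and the sampling are untouched. Because the text is operative and concerns a primary outcome, it should be corrected even if the cause is a slip.

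**What to change.** 1. Reconcile the probe sentence with the one before it. State a separate probe for CEA, for CK20 and for actin, and assign the ACTB probe to actin only.
2. Choose one quantity and define it. If the level is meant, write 2^-ΔCt with ΔCt = Ct target - Ct actin for each sample. If a fold change is meant, keep 2^-ΔΔCT, define both ΔCt terms and name the calibrator sample, for example the patient's own first sample from the same site.

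The cost is a correction to the protocol text and, if it carries the same wording, to the laboratory manual. No patients, samples or additional assays are needed. If assays have already been run, the record of the probes used should be checked against the corrected text.

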**Fig. 7 Fig7:**
[figure not shown]
Example template of recommended content for the schedule of enrolment, interventions, and assessments

## Discussion

Since total mesorectal excision (TME) has been accepted worldwide, the survival from rectal cancer has significantly improved, and is even better than for colon cancer in some countries [14–17]. In 2007, CME with CVL for colon cancer was suggested in Western countries which follows similar oncological principles as TME does for rectal cancer [6]. The principles of CME require resection of the affected colon with its associated lymphovascular supply through complete removal of the mesocolon as an envelope to minimize the risk of spillage of tumor cells into the peritoneal cavity and central ligation of the vascular supply at its origins to increase lymph node harvest. In a series of studies, CME has shown an improved survival and reduced local recurrence when compared with standard surgery [7, 8, 18, 19].

Realizing that removing draining lymph nodes potentially eliminates the probability of leaving behind residual disease, which has implications for local control and survival, more emphasis is placed on lymphadenectomy in Eastern countries. Moreover, a D3 extended lymphadenectomy is considered the standard of care for clinical stage II and III colon disease in Asian countries, especially in Japan [20]. Actually, both CME and D3 lymphadenectomy follow the same oncological principles, mainly including excision of the mesocolon within an intact fascial envelope and central vascular ligation. Furthermore, both techniques have shown impressive outcomes as compared with standard excision.

For left-sided colon cancer, exposure and ligation the origin of the inferior mesenteric artery is not difficult, as the TME principles are commonly followed. However, in order to identify the origins of the vessels supplying the right-side colon and perform true D3 lymphadenectomy, the head of the pancreas, the anterior surface of the SMV, and the superior mesenteric artery (SMA) should be fully exposed, which are all technical challenges and more traumatic, leading to longer operation times than the standard operation [21, 22]. The original CME initially described by Hohenberger was performed via a laparotomy. Due to laparoscopic surgery with short- and long-term benefits, there are a series of studies looking at the feasibility of laparoscopic-CME especially for right colon cancer. Finally, although these studies have shown the feasibility and safety of this procedure with acceptable morbidity and oncological outcomes, laparoscopic right hemicolectomy with CME and true center vascular ligation for right colon cancer remains technically challenging especially for obese patients [9, 22, 23].

Since HALS returns the sense of touch to the surgeon, this procedure may represent a valid alternative approach to standard laparoscopy. Furthermore, HALS has been shown to eliminate a substantial part of the technical challenges of standard laparoscopy along with having an acceptable learning curve and reducing operative time, but patient morbidity rates and recovery are comparable with standard laparoscopy [12, 13]. However, this HALS technique allows for hand assistance during laparoscopic surgery and tactile sensation of the lesion, and people argue that this approach is against the “no-touch” isolation technique.

The virtue of the “no-touch” isolation technique is another controversial issue in the field of colorectal disease. In 1952, Barnes first described and adopted a special technique for resection of right colon cancer: ligation of the vascular pedicles and division of the bowel before handling the cancer-bearing segment [24]. This special technique was first named a “no-touch” isolation technique by Turnbull in 1953, based on previous clinical and basic research [25]. The aim of this technique is to reduce cancer cells flowing from the primary tumor site to the liver and other organs by ligation of the vascular pedicles first. However, since then, the value of the “no-touch” technique in colon surgery has always been debated. In a retrospective analysis, although Turnbull et al. had demonstrated that “no-touch” isolation resection could greatly improve survival rates compared with conventional manipulative resection, these results might be due to more extended resections in the no-touch group [25]. The only prospective randomized controlled trial did suggest a limited benefit of the “no-touch” isolation technique with regard to the overall survival, and a tendency for reduction in occurrences of liver metastases [26]. Another randomized controlled trial is currently underway in Japan to demonstrate the superiority of the special technique (JCOG1006) [27]. Whether surgical manipulation of the cancer-bear segment would increase the detachment and circulation of tumor cells into the peripheral circulation is also still debated. Hayashi et al. [28] demonstrated that the “no-touch” isolation technique may prevent cancer cells from being shed into the portal circulation by using mutant-allele-specific amplification, while Garcia-Olmo et al. [29] found CEA products only in one of eighteen patients who underwent conventional surgery by using RT-PCR.

In this trial, the novel HALS-CME procedure, which takes full advantages of the HALS technique and potential “no-touch” isolation technique, has several technical merits:After transecting the distal ileum and its mesentery, the distal end of the superior mesenteric vessels are easily exposed, especially for obese patients.Transecting the transverse colon and returning the two ends back into peritoneal cavity, the neck of the pancreas can be easily observed and be a landmark during lymph node dissection along the left and surface of the SMV, which is true D3 lymphadenectomy.It is well known that there are fewer venous branch drains into the left of the SMV; dissection along the left axis of the SMV in a repeated unidirectonal/longitudinal manner facilitates location and ligation of the root of the ileocolic vessels, right colic vessels, and Henle’s trunk, avoiding injuring these branches.After vascular pedicles, the transverse colon, and the distal ileum are ligated, the cancer-bearing segment is manipulated from medial to lateral, which is more consistent with the “no-touch” isolation technique described by Barnes [24]. The total “no-touch” isolation technique appears to have potential benefits for decreasing tumor cells spreading into the portal vein and circulatory system during the operative manipulation.After transecting the bowel and ligating feeding vessels, the medial to lateral approach is adopted to avoid direct contact with the tumor. The surgeon’s hand provides better retraction for mobilization of the involved colon and dissection along the Toldt’s fascia, which shortens the operation time.

There are potential limitations in this trial. 1) The trial will be carried out in only one center, which may impact participant recruitment and limit the applicability of the outcomes to other centers. 2) The open-label nature of the trial may cause biased estimates of the treatment effect. However, it is not possible to blind the surgeon for the special nature of nonpharmacologic trials. Although the surgeons, researchers, and participants are not blinded, the pathologists, statisticians, and follow-up staff will be blinded to the group assignment, which contributes to reducing the treatment effect estimation bias. 3) The relatively short follow-up time has an impact on comparing long-term outcomes. In summary, if the feasibility, short-term safety, long-term oncological safety, and potential total “no-touch” isolation technique benefits of HALS-CME are verified, this technique could be recommended as a new approach to overcome the technical challenges in right hemicolectomy for right colon cancer.

## Trial status

This trial was initiated in December 2015 and is currently recruiting patients.

## Abbreviations

AJCC: American Joint Committee on Cancer
ASA: American Society of Anesthesiologists
CA19-9: Carbohydrate antigen 19-9
cDNA: Complementary DNA
CEA: Carcinoembryonic antigen
cLAP: Conventional laparoscopic surgery with CME and D3 lymphadenectomy
CME: Complete mesocolic excision
CONSORT: Consolidated Standards of Reporting Trials
CRF: Case report form
CRP: C-reactive protein
CT: Computed tomography
CVL: Central vascular ligation
DFS: Disease-free survival
ECOG: Eastern Cooperative Oncology Group
HALS: Hand-assisted laparoscopic surgery
HALS-CME: Hand-assisted laparoscopic surgery with complete mesocolic excision, D3 lymphadenectomy, and total “no-touch” isolation
IL: Interleukin
LAP-CME: Laparoscopic surgery with CME, D3 lymphadenectomy, and total “no-touch” isolation
NCCN: National Comprehensive Cancer Network
OS: Overall survival
PBS: Phosphate-buffered saline
PCT: Procalcitonin
PFS: Progression-free survival
RT-PCR: Real-time polymerase chain reaction
SMA: Superior mesenteric artery
SMV: Superior mesenteric vein
TEM: Total mesorectal excision
